## 2. Methodology

### 2.1. Trial Design

This is a single-centre double-blind study of the effects of mixed air pollutants on the cognitive function of healthy human volunteers with a family history of increased risk of dementia. Participants will all undertake sequential controlled exposures to four air pollutants and clean air as control exposure, i.e., a repeated measures design. Cognitive testing, biological sampling, and physiological tests will be carried out before and after each exposure. The study design is outlined in Figure 1.

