#### 2.3.5. Participant Safety and Anonymity

All participants enrolled in this study will be allocated a unique anonymous identifying code which will appear on all data collection documents. The hard-copy case report forms (hCRF) and source data files (SDF) will be kept within a locked room. All electronic data will be stored on secure password-protected servers with limited access to members of the research team.

Participant eligibility will be reviewed at the beginning of each visit (separated by a minimum two-week washout period) prior to air pollution exposure. Participation will be discontinued for those who do not match the eligibility criteria when reviewed.

The checking for the occurrence of adverse events (AEs) will begin from enrolment and will continue for the individual participant until their last visit. At each study visit, the researcher will assess eligibility and recent clinical history including the occurrence of adverse or serious adverse events (SAEs). Details of adverse and clinical events will be captured on the trial hCRF and eCRF. All SAEs will be recorded in the hospital notes, the eCRF, the hCRF, and the Sponsor’s SAE Recording Log. All SAEs will be reported to the Sponsor via the Research Office (RO) dedicated mailbox on an SAE form and the SAE Log will be sent to Sponsor on request. The PI will complete the Sponsor’s SAE form and the form will be sent within 24 hours of the Investigator becoming aware of the event. The PI will respond to any SAE queries raised by the Sponsor as soon as possible.

Expected Adverse Reactions are possible short-term respiratory symptoms such as cough/shortness of breath to susceptible individuals. We will minimise this risk by assessing the participants pre-enrolment onto the study for respiratory conditions. We will also conduct safety measures such as spirometry and exclude individuals with abnormal results which may also suggest a high risk to pollutant exposure. Investigators will complete the appropriate SAE form on the eCRF and an automatic email notification will be sent to the Trial Manager, PI and Sponsor.

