#### 2.5.2. Blood Tests

Blood will be taken as part of the assessment of inflammatory response. This will be plasma and RNA samples 5 mL (3 bottles pre exposure and 3 bottles on visit b), a total of 30 mL per participant per visit.

These collected samples will be centrifuged and transported to Imperial College Health Care NHS trust for analysis and storage. These will be stored for 2 years under their Human Tissue Authority License number 12,275.

Once analysis has been completed, any additional samples will be stored in biobanks for up to 30 years if participants have consented to this optional/additional section in the ICF. If a participant does not wish to have their samples stored in a biobank, this will not affect their participation in the study. It is expected that these biobanked samples will be accessible to researchers for further analysis in the future.

We intend to complete analyses for the following effects. Systemic inflammation will be assessed by measuring plasma concentrations of TNF-
α
, IL6, IL8, and C-reactive protein (CRP). BBB disruption, neuroinflammation, and neuronal injury will be assessed by determination of S100 calcium-binding protein B (S100B), Glial fibrillary acidic protein (GFAP), and Neurofilament light chain (NF-L), respectively, using commercial ELISAs.

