**Figure 2 ijerph-21-00284-f002:**
[figure not shown]
The two-way valve and mask set-up during exposure. Black arrows show airflow direction of one-way valves. Participants inhale air from the chamber (red line) and exhale into the surrounding room (dark grey line).

**Table 1 ijerph-21-00284-t001:** Study time schedule of enrolment, exposures, and visits. Exp = Exposure.

	Recruitment		Enrolment		Post-Enrolment						
			**First Wave (W1)**	**Second Wave (W2)**	**Exp 1 (W1)**	**Exp 2 (All)**	**Exp 3 (All)**	**Exp 1 (W2)**	**Exp 4 (All)**	**Exp 5 (All)**	**Remnant Exp(s)**
Start date		09-Jan-23	02-May-23	01-Jun-23	15-May-23	19-Jun-23	24-Jul-23	21-Aug-23	11-Sep-23	16-Oct-23	20-Nov-23
End date		30-Jun-23	31-May-23	30-Jun-23	02-Jun-23	07-Jul-23	11-Aug-23	25-Aug-23	29-Sep-23	03-Nov-23	30-Nov-23
ENROLMENT											
Information Sheet		X									
Informed Consent			X	X							
Eligibility Screen			X	X	X	X	X	X	X	X	X
VISITS											
Exp 1	Visit A				X			X			X
	Visit B				X			X			X
Exp 2	Visit A					X					X
	Visit B					X					X
Exp 3	Visit A						X				X
	Visit B						X				X
Exp 4	Visit A								X		X
	Visit B								X		X
Exp 5	Visit A									X	X
	Visit B									X	X
MEASURES											
Pre-Exposure					X	X	X	X	X	X	X
Post-Exposure					X	X	X	X	X	X	X

**Table 2 ijerph-21-00284-t002:** Summary of the cognitive tasks completed by participants pre and post exposure. Tasks will be administered in table order, starting with the Spatial *n*-back Task (SNB).

Task	Outcome Metrics	Cognitive Domain	Duration
Spatial *n*-back Task (SNB)	Working memory ability	Learning and memory	10 min
Face Identification Task (FIT)	Distractor suppression	Executive function	15 min
	Cognitive control		
Purdue Pegboard Test (PPT)	Gross movements of arms, hands, and fingers	Perceptual-motor function	10 min
	Fine motor extremity		
Expression Recognition Task (ERT)	Expression Discrimination	Socio-emotional cognition	15 min
	Approach bias		
Psychomotor Vigilance Task (PVT)	Sustained attention/vigilance	Attention	10 min
	Psychomotor speed		

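### Active adverse-event checking ends at the last visit, so each participant's last exposure is followed only to its own Visit B, while every earlier exposure is asked about again at least two weeks later

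*Protocol article*

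**What the plan says.** Section 2.3.5 (Participant Safety and Anonymity) fixes both the period and the method of adverse-event collection. Checking "will begin from enrolment and will continue for the individual participant until their last visit". The method is enquiry at visits: "At each study visit, the researcher will assess eligibility and recent clinical history including the occurrence of adverse or serious adverse events (SAEs". The same section places the washout between visits, "separated by a minimum two-week washout period) prior to air pollution exposure", and names the reactions it anticipates: "Expected Adverse Reactions are possible short-term respiratory symptoms such as cough/shortness of breath to susceptible individuals".

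Section 2.1 gives every participant five exposures: "Participants will all undertake sequential controlled exposures to four air pollutants and clean air as control exposure, i.e., a repeated measures design". Section 2.5.2 shows that Visit B comes after the exposure, since blood is drawn as "3 bottles pre exposure and 3 bottles on visit b".

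Table 1 ("Study time schedule of enrolment, exposures, and visits") gives each exposure a Visit A and a Visit B. Under its "Post-Enrolment" heading the columns are the exposure windows and a final catch-up window for remnant exposures. No visit or contact is listed after that.

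**The concern.** Events are found by asking at visits, so how long an exposure is watched depends on whether another exposure follows. Earlier exposures get a second enquiry after the washout. The last one does not.

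Two things are at stake. First, a delayed event that is not among the expected short-term reactions could follow the last exposure without anyone being scheduled to ask about it. Second, a simple count of adverse events by exposure would set periods of at least two weeks beside a much shorter one, so an exposure that often came last could look better tolerated only because it was watched for less time. This is a stated rule with a stated end point, not a detail that a condensed article has left to the full protocol.

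**Working it through.** **Inputs**
- Participants: 15, the revised target (sections 2.3 and 3).
- Exposures per participant: 5 (section 2.1).
- Minimum washout: 14 days (section 2.3.5).
- Assumed dropout: 33% (section 3), so 0.33 × 15 = 4.95, about 5 participants.
- Exposure windows: the dates in Table 1.
- Interval from exposure to Visit B: not given in the text. It may be in Figure 1, which is not shown.

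The plan gives no figure of its own to reproduce on this point.

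**Step 1. Could Visit B itself fall two weeks after the exposure?** Read literally, section 2.3.5 attaches the washout to each visit, which could put Visits A and B two weeks apart. Table 1 rules this out. The Exp 1 window for wave 2 runs from 21 to 25 August 2023 and holds both visits, so they are at most 4 days apart there. The washout must lie between exposures.

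**Step 2. When is an earlier exposure asked about again?** Gaps from the end of one window to the start of the next:

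| Transition | Gap |
|---|---|
| Exp 1 (W1) to Exp 2 | 17 days |
| Exp 2 to Exp 3 | 17 days |
| Exp 3 to Exp 4 (wave 1) | 31 days |
| Exp 3 to Exp 1 (wave 2) | 10 days |
| Exp 1 (W2) to Exp 4 | 17 days |
| Exp 4 to Exp 5 | 17 days |
| Exp 5 to remnant window | 17 days |

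The 10-day gap is 14 days from window end to window end, so an individual can still be given two weeks. With the washout rule, every non-final exposure is followed by another enquiry at least 14 days later.

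**Step 3. When is the last exposure asked about again?** It is not. No check is scheduled after its Visit B. A participant who uses the remnant window does get a later check on the exposure before it, but the remnant exposure then becomes the last one.

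**Step 4. How many exposures are affected?** Each participant has exactly one last exposure.
- All complete: 15 / (15 × 5) = 15/75 = 20%.
- Five withdraw after one exposure each: 15 / (10 × 5 + 5 × 1) = 15/55 = 27%.
- Five withdraw after four exposures each: 15 / (10 × 5 + 5 × 4) = 15/70 = 21%.

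The withdrawal figures assume that the five leave without attending another visit. Someone discontinued at the eligibility review of a later visit would be asked about events at that visit.

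**Step 5. How short is the last window? (illustration only)** If Visit B falls f days after the exposure, active checking covers f/14 of the minimum that the other exposures get: 1/14 = 7%, 2/14 = 14%, 4/14 = 29%. The 4-day case is the most that the August window allows. All three values of f are assumptions.

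**The case against.** The strongest reply is that the window suits its purpose. Each exposure is a single 60-minute session at rest, the expected reactions are short-term, and Visit B still follows the last exposure. Section 2.4 adds that a review of chamber studies at higher concentrations found no evidence of adverse events. Most of this stands, and it limits the gap to events arising after Visit B. The review covers wood smoke and diesel exhaust only, though, not cooking emissions or the limonene aerosol. Nor does the reply explain why the last exposure should be watched for less time than the others.

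A reader might also infer more than the documents support:
- **That a planned comparison is biased.** Section 2.7 lists cognitive tasks, inflammatory or immune signals, lung function and DNA as end points. Adverse events are not among them, and no comparison of them by pollutant is stated. The unequal time matters for safety reporting, not for a declared analysis.
- **That dropout adds about five more affected exposures.** It does not. Those participants' last exposures are already among the 15; dropout only reduces the denominator.
- **That the shortfall falls on one pollutant.** Table 1 puts Exp 1 after Exp 3 for wave 2, which hints that the labels name particular exposures, with Exp 5 usually last. The article does not say how sequences are allocated, so this remains an inference. The last exposure may also be clean air.
- **That serious events after the last visit go unreported.** The 24-hour SAE form runs from the investigator becoming aware, and neither it nor the SUSAR timelines are stated to end at the last visit. What ends is active enquiry.

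Finally, section 2.3.5 asks about recent history without defining how far back. The two-week figure for earlier exposures is therefore the spacing of enquiries, not a declared look-back period.

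**Conclusion.** The point holds as an unequal ascertainment window built into a stated rule. One exposure per participant is actively checked only to its own Visit B: 20% of exposures if all 15 complete, 21% to 27% under the plan's own dropout assumption. This rests on reading the washout as lying between exposures, which Table 1 requires, and on Table 1 listing every scheduled contact. How many days are lost cannot be fixed without the exposure-to-Visit B interval, and which source, if any, bears the loss cannot be determined. The primary and secondary end points in section 2.7 are not touched. It is a worthwhile, inexpensive improvement to safety ascertainment, not a threat to the trial's main conclusions.

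**What to change.** In section 2.3.5 and Table 1, bring the end of adverse-event checking into line with the interval that the other exposures receive. Add one brief remote contact after the last exposure actually received, for those who withdraw as well as those who complete. The investigators should set its timing.

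Separately, tabulate adverse events by exposure over one common post-exposure window, for example to Visit B, and report later events apart from that table. This makes the counts comparable whatever the order of exposures.

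The contact costs about 15 short calls or messages by existing staff and a wording change, with no new sample or procedure. The tabulation needs no new data. It remains possible if data collection has already closed, which matters because the article expected collection to finish by the end of 2023.

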#### 2.3.4. Participant Blinding

This will be a double-blind study with both the trial participants and researchers/care staff responsible for data collection and analysis (MCRF staff; [name]; and [name]) blinded to the exposure. Other investigators will not be blinded as to the order of exposures. Participants will be informed about the five pollution exposures, but the sequence in which they encountered them will remain undisclosed. To assess potential unblinding among trial participants, the (unblinded) MAC team will ask participants to indicate which of the five exposures, including clean air, they believe they encountered following each one-hour exposure. Furthermore, participants will be asked to provide a confidence judgment along with their response. Trial participants and data collection staff will also be blinded during data analysis.

The PI will make the decision to un-blind the current participant exposure in the case of a serious adverse event (SAE) when knowledge of the chemical composition of the exposure is vital for appropriate clinical management or the participant’s well-being.

While there is a risk of unblinding due to smell, adding scents to mask pollutants or using external agents like menthol nasal rubs poses separate challenges, including potential alterations in the pollutant mixture and their impact on airway dilation, introducing additional confounding factors.

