A Suspected Unexpected Serious Adverse Reaction (SUSAR) is an adverse reaction that is classed as both serious and unexpected. The Trial Manager will ensure that SUSAR reports are un-blinded and reviewed by the PI or designee within 2 days and adjudicate whether the event constitutes a SUSAR. The Trial Manager will ensure that fatal or life-threatening SUSARs are reported to UREC as soon as possible, but no later than 7 calendar days after the receipt of the eSAE report. Any additional information will be reported within 8 days of sending the first report.

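### Suspected SUSARs are unblinded before anyone decides whether they are SUSARs, and without the clinical-need test the protocol sets for unblinding other serious events

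*Protocol article*

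**What the plan says.** Two places in the protocol article govern unblinding after a serious event.

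- **Section 2.3.4 (Participant Blinding).** After a serious adverse event (SAE), the PI decides whether to decode the exposure, and does so "when knowledge of the chemical composition of the exposure is vital for appropriate clinical management" or for the participant's well-being. Participants and the staff who collect and analyse data are blinded. Other investigators are not, and neither is the chamber team.
- **Section 2.3.5 (Participant Safety and Anonymity).** A SUSAR "is an adverse reaction that is classed as both serious and unexpected". The Trial Manager ensures that "SUSAR reports are un-blinded and reviewed by the PI or designee within 2 days and adjudicate whether the event constitutes a SUSAR". No clinical-need condition is attached.

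Section 2.3.5 also sets the reporting times. The PI completes the Sponsor's SAE form, and "the form will be sent within 24 hours of the Investigator becoming aware of the event". Separately, "Investigators will complete the appropriate SAE form on the eCRF and an automatic email notification will be sent" to the Trial Manager, PI and Sponsor. Fatal or life-threatening SUSARs go to the ethics committee as soon as possible and "no later than 7 calendar days after the receipt of the eSAE report".

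**The concern.** Whether a serious event counts as a suspected reaction is partly a matter of opinion, and that opinion is open to influence by the exposure. Someone who knows that the session was clean air has an obvious reason to call the event unrelated. Someone who knows that it was diesel exhaust has a reason to call it related. If the code is broken first, the comparison of suspected reactions between clean air and the pollutants may partly reflect what the adjudicator knew.

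There is also an avoidable loss of blinding. The stated order decodes every report that reaches this step, including those then found not to meet the definition. For these, the decoding served neither care nor reporting. This sits awkwardly beside Section 2.3.4, where unblinding after an SAE is an exception tied to need.

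**Working it through.** No sample size, power or error rate enters this point. The check is a comparison of the stated rules, with one short sum on the reporting times.

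**1. Order of steps.** The Section 2.3.5 sentence lists unblinding, then review, then adjudication. The outcome of adjudication is whether the event is a SUSAR at all, so that question is open when the exposure is decoded.

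**2. What adjudication covers.** By the article's definition a SUSAR must be (a) an adverse reaction, (b) serious and (c) unexpected. An event becomes a reaction only if it is attributed to the exposure, so (a) is a judgement of relatedness. The article describes no earlier, blinded judgement of relatedness.

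**3. Whether the code is needed to adjudicate.** Seriousness does not depend on which exposure was given. On expectedness, Section 2.3.5 gives one description of expected reactions (short-term respiratory symptoms) and does not divide it by pollutant. Relatedness can be judged on the premise that a pollutant was given. On the article's own terms, none of the three requires the code.

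**4. The two rules side by side.**

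| | Section 2.3.4 | Section 2.3.5 |
|---|---|---|
| Trigger | an SAE | a SUSAR report |
| Condition | vital for care or well-being | none |
| Who decides | PI, case by case | automatic, ensured by the Trial Manager |
| Timing | when needed | before adjudication |

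Every SUSAR is by definition serious, so an event reaching the second rule also falls under the first. The article does not say how the two fit together.

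**5. Reporting time.** The inputs are the 24-hour (1-day) limit for the Sponsor's form and the 7-day limit from receipt of the eSAE report, a term the article does not define.

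- If the eSAE report is the Sponsor's form, or the eCRF form is held to the same limit: 1 + 7 = 8 days at most from awareness to the ethics report. This is a different quantity from the 8 days allowed for follow-up information.
- If it is the eCRF form and the 24-hour limit does not cover it: x + 7 days, where x is not given. Assumed values of x = 0, 1, 7 and 14 days give 7, 8, 14 and 21 days.
- The start of the 2-day review is not stated. If it runs from receipt, 7 − 2 = 5 days remain after adjudication. Decoding could follow adjudication within that time.

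**The case against.** **The reports may already be suspected reactions.** Section 2.3.5 speaks of SUSAR reports, not of all SAEs. Relatedness might be recorded on the SAE form before the code is broken, leaving only confirmation or expectedness to settle. This is possible, but the article mentions no such entry, and the same sentence leaves the SUSAR decision to be made. The objection limits how firmly bias can be asserted. It does not remove the sequence.

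**The adjudicator may already know the exposure.** Investigators outside the blinded group know the order of exposures, and the PI's own status cannot be read because names were removed. If the PI is unblinded, the stated order changes nothing for the PI. This stands, and the point therefore applies only where the PI or designee is otherwise blind. Nor does anything in Section 2.3.5 pass the exposure to participants or to those who assess outcomes.

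**The two rules may serve different purposes.** One concerns care and the other reporting, and Section 2.3.4 does not claim to be the only route. That is a fair reading, but reporting needs the code only once an event has been found to be a SUSAR.

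**Stronger readings that the document does not support.**

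- *One decoding could reveal a whole exposure window, for up to 15 participants.* Table 1 schedules the second wave for exposures 2 and 3 before its exposure 1, which might suggest that each number denotes one fixed pollutant. The table never says so. It also gives exposure 1 separate windows for the two waves and adds a window for remaining exposures.
- *The reporting time has no upper limit, or an event can be reported late within the rules.* The first holds only if the eSAE report is the eCRF form and falls outside the 24-hour limit. The second needs a standard for lateness that the article does not give. The article also asks for reporting as soon as possible, and a condensed article commonly leaves form definitions to the full protocol.

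**Conclusion.** The point holds in a limited form. As written, Section 2.3.5 decodes SUSAR reports before the SUSAR judgement and without the need test in Section 2.3.4. Where the adjudicator is otherwise blind, that judgement, including whether the event is a reaction, is made knowing the exposure. Events judged not to be SUSARs are then unblinded to the adjudicator without need.

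This rests on two assumptions: that the PI or designee is not already unblinded, and that relatedness has not been settled blind beforehand. The article confirms neither.

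The practical size is small. The revised target is 15 participants screened as healthy, and Section 2.4 reports no evidence of adverse events in earlier wood smoke and diesel studies at higher concentrations. Few events are expected, although that review does not cover the cooking and cleaning-product exposures. No efficacy endpoint, analysis or sample size is affected.

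The undefined eSAE term is a minor clarification and not a separate fault.

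**What to change.** Reconcile Sections 2.3.4 and 2.3.5:

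1. The PI or designee judges seriousness, relatedness and expectedness blind, as if a pollutant had been given.
2. Only an event that meets the SUSAR definition is then unblinded for reporting. The chamber team already holds the code and can supply it.
3. Emergency unblinding under Section 2.3.4 stays unchanged.
4. State whether the PI and any designee are blinded to exposure order. If neither is, name a blinded adjudicator or acknowledge that the judgement is unblinded.
5. As a clarification, name the form meant by the eSAE report and say whether the 24-hour limit covers it. If it does, the maximum from awareness to the ethics report is about 8 days.

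The cost is a few sentences in the safety section. No extra data are needed, and no extra staff unless a blinded adjudicator has to be named. The sponsor would also need to say how an event is handled if it meets the definition blind and then proves to have followed clean air.
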